# Effects of sodium-glucose co-transporter 2 inhibitors on ultrafiltration in patients with peritoneal dialysis: a protocol for a randomized, double-blind, placebo-controlled, crossover trial (EMPOWERED)

**DOI:** 10.1007/s10157-024-02467-w

**Published:** 2024-02-25

**Keywords:** SGLT2 inhibitor, Peritoneal dialysis, Ultrafiltration, Volume overload

## Abstract

**Background:**

Volume overload is common and associated with high mortality in patients on peritoneal dialysis (PD). Traditional strategies including diuretics, water/salt restriction, and icodextrin-based solutions cannot always fully correct this condition, necessitating novel alternative strategies. Recent studies confirmed the expression of sodium–glucose cotransporter 2 (SGLT2) in the human peritoneum. Experimental data suggest that SGLT2 inhibitors decrease glucose absorption from the PD solution, thereby increasing the ultrafiltration volume. This trial aims to assess whether SGLT2 inhibitors increase the ultrafiltration volume in patients on PD.

**Methods:**

The EMPOWERED trial (trial registration: jRCTs051230081) is a multicenter, randomized, double-blind, placebo-controlled, crossover trial. Patients with clinically diagnosed chronic heart failure are eligible regardless of the presence of diabetes if they use at least 3 L/day glucose-based PD solutions. Participants will be randomly assigned (1:1) to receive empagliflozin 10 mg once daily and then placebo or vice versa. Each treatment period will last 8 weeks with a 4-week washout period. This study will recruit at least 36 randomized participants. The primary endpoint is the change in the daily ultrafiltration volume from baseline to week 8 in each intervention period. The key secondary endpoints include changes in the biomarkers of drained PD solutions, renal residual function, and anemia-related parameters.

**Conclusions:**

This trial aims to assess the benefit of SGLT2 inhibitors in fluid management with a novel mechanism of action in patients on PD. It will also provide insights into the effects of SGLT2 inhibitors on solute transport across the peritoneal membrane and residual renal function.

**Supplementary Information:**

The online version contains supplementary material available at 10.1007/s10157-024-02467-w.

## Introduction

Peritoneal dialysis (PD) is an established renal replacement therapy, based on the exchange of water and solute between capillary blood and dialysate fluid across the peritoneal membrane, and 11% of patients undergoing dialysis worldwide are on PD [1]. Given the link between volume overload and poor outcomes, encompassing both technical survival and mortality in patients on PD [2], adequate ultrafiltration, relying on the osmotic gradient typically induced by the hypertonic glucose concentration, is a crucial element for successful PD therapy. Ultrafiltration and the volume status are closely interrelated, and in fact, several studies reported that higher ultrafiltration volume was associated with better prognosis in patients on PD [3, 4]. The glucose gradient peaks at the start of dialysis but diminishes as glucose diffuses into blood. In patients with greater peritoneal vascularity in particular, it is difficult to achieve adequate ultrafiltration because the glucose gradient diminishes more rapidly [5]. One typical strategy in this setting is to use a PD solution with higher glucose content to obtain a higher glucose gradient. However, this strategy might be ineffective because of enhanced fluid intake attributable to hyperglycemia, and it can lead to more rapid damage to the peritoneal membrane, resulting in the discontinuation of PD therapy [6].

Recent studies confirmed the expression of sodium–glucose cotransporter 2 (SGLT2) in the human peritoneum [7–9]. Animal studies demonstrated that SGLT2 inhibitors increased ultrafiltration potentially through the maintenance of the glucose gradient upon the inhibition of SGLT2 activity in the peritoneum, although conflicting results exist [7, 9, 10]. In addition, SGLT2 inhibitors were reported to mitigate peritoneal fibrosis and angiogenesis, both of which contribute to ultrafiltration failure, in a mouse model [8, 11]. Based on this information, we hypothesized that SGLT2 inhibitors might increase the ultrafiltration volume and improve long-term prognosis in patients on PD by correcting volume overload and mitigating peritoneal tissue damage. Because there is little information on the use of SGLT2 inhibitors in patients on PD, we decided to first evaluate the effect of SGLT2 inhibitors on the ultrafiltration volume in short-term interventions.

## Methods

### Study design

The EMPOWERED trial is a multicenter, randomized, double-blind, placebo-controlled, crossover trial evaluating the efficacy and safety of once-daily oral empagliflozin 10 mg in patients on PD. This trial has been registered at the Japan Registry of Clinical Trials (jRCTs051230081). The trial was approved by the Osaka University Clinical Research Review Committee (approval number: S23004), and it is being conducted according to the 1964 Declaration of Helsinki and its later amendments or comparable ethical standards. This trial will be conducted at four academic and community hospitals in Japan (i.e., Osaka University Hospital, National Cerebral and Cardiovascular Center, Osaka General Medical Center, and Matsuyama Red Cross Hospital). Written, informed consent will be obtained from all individual participants included in the study. The trial is being managed by the Academic Clinical Research Center of Osaka University Hospital with the cooperation of intellim Corporation, a Contract Research Organization, which is responsible for monitoring, data management, and statistical analysis. This trial received funds from Nippon Boehringer Ingelheim Co., Ltd. and Eli Lilly Japan K.K. under a research agreement with Osaka University. Boehringer Ingelheim Pharma GmbH & Co. KG is providing drugs for the study. This study was collaboratively designed with input from both academic members and representatives from Nippon Boehringer Ingelheim. Patient enrollment will be started in December 2023, and the scheduled completion date is October 2024.

### Study participants

Enrolled participants must meet all inclusion criteria and none of the exclusion criteria listed in Table 1. Key inclusion criteria include an age of 18–90 years, PD vintage ≥ 3 months, use of ≥ 3 L/day glucose-based PD solution, and a diagnosis of and treatment for chronic heart failure. The Japanese Ministry of Health, Labor, and Welfare had approved empagliflozin for the treatment of type 2 diabetes and chronic heart failure at the time of manuscript submission. However, because of a lack of efficacy in the hypoglycemic effect, empagliflozin is not approved for type 2 diabetes in patients on dialysis in Japan. Therefore, inclusion criteria for chronic heart failure were established to conduct the study under the approved indications in Japan. These include elevated N-terminal pro-brain natriuretic peptide (NT-proBNP)/brain natriuretic peptide (BNP) levels, structural heart disease, elevated left ventricular filling pressure, or a history of hospitalization for heart failure. The definitions of structural heart disease and elevated filling pressure are presented in Supplementary Table 1. Key exclusion criteria include treatment with SGLT2 inhibitors within 3 months of enrollment, hybrid therapy with PD and hemodialysis, and peritonitis within 2 months of enrollment. These criteria were selected because rapid ultrafiltration by hemodialysis and peritonitis can alter peritoneal function.

**Table 1 Tab1:** Inclusion and exclusion criteria

Inclusion criteria	Age ≥ 18 and ≤ 90 years BNP ≥ 40 pg/mL, NT-proBNP ≥ 400 pg/mL, structural heart disease (left atrial enlargement and/or left ventricular hypertrophy), elevated filling pressures, or a history of hospitalization for heart failure* Standard medical therapy for heart failure (at least one of the following: loop diuretics, ACEIs, ARBs, ARNIs, beta-blockers, or MRAs) PD vintage ≥ 3 months Glucose-based PD solution use ≥ 3 L/day Voluntarily participate with written informed consent
Exclusion criteria	Treatment with SGLT2 inhibitors within 3 months before enrollment Individuals who are not expected to survive more than 1 year after enrollment On a hybrid therapy comprising peritoneal dialysis and hemodialysis Individuals who have or have had peritonitis within the past 2 months Women who are pregnant or nursing Active infections Individuals who participate in clinical studies (trials and research) involving other interventions Individuals disqualified from participation in the study by the investigator or sub-investigator for any other reasons

*NT-proBNP must be used to confirm eligibility for participants receiving ARNIs

*BNP* brain natriuretic peptide; *NT-proBNP* N-terminal pro-brain natriuretic peptide; *ACEIs* angiotensin-converting enzyme inhibitors; *ARBs* angiotensin receptor blockers; *ARNIs* angiotensin receptor neprilysin inhibitors; *MRAs* mineralocorticoid receptor antagonists; *PD* peritoneal dialysis; *SGLT2* Sodium-Glucose Cotransporter 2

### Randomization

The participants will be randomized to the empagliflozin or placebo group at a 1:1 ratio. This allocation will be executed utilizing a computer-generated random sequence and will be stratified by study sites, using a permuted block randomization method. Because the study is double-blinded, patients, their families, the study team, and the sponsor will not have access to the randomization information until the trial database is locked.

### Intervention periods

Figure 1 displays a scheme for this trial. The study includes a two-period crossover consisting of 8 weeks of treatment and a 4-week washout between treatment periods. Participants will visit every 4 weeks and continue on trial medication, namely empagliflozin 10 mg or placebo, once daily, in each period. The utilization of SGLT2 inhibitors, excluding empagliflozin, is strictly proscribed, and changes in PD prescriptions are fundamentally prohibited. Adherence to the study drugs will be monitored by interviewing the patients at every visit and counting tablets at the end of each period. Table 2 presents the observation and evaluation schedule during the study period.

**Fig. 1 Fig1:**
[figure not shown]
Study scheme. Participants will be randomized to receive empagliflozin 10 mg once daily and then placebo or vice versa. Each treatment period will last 8 weeks, with a 4-week washout period in between. After randomization, patients will visit every 4 weeks during the study period

**Table 2 Tab2:**
[figure not shown]
Observation, test, and evaluation schedule

*NT-proBNP*, N-terminal pro-brain natriuretic peptide; *BNP* brain natriuretic peptide; *FAST PET* frequently and short time peritoneal equilibration test; *KIM-1* kidney injury molecule 1

●, required; ○, if necessary

*Data collected from routine medical practice 182 days before providing informed consent may be used for assessment

**Data collected from routine medical practice 365 days before providing informed consent may be used for assessment

***Urine KIM-1 is measured only on Visit 3 and Visit 6

### Primary endpoint

The primary endpoint of the study is the change in the daily ultrafiltration volume from baseline to week 8 in each intervention period. The ultrafiltration volume from non-glucose-based PD solution (i.e., icodextrin-containing PD solution) will be excluded. The daily ultrafiltration volume will be calculated as the mean of all results for 5 of 7 consecutive days, after excluding the maximum and minimum values. The participants will record data for each session including the type of PD solution, dwell time, and instilled/drained volume of the PD solution.

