### Sample size calculation

Our preliminary data revealed an average increase in the daily ultrafiltration volume from the glucose-based PD solution of 90 mL/day in five patients on PD who received 10 mg of empagliflozin and used at least 3 L/day glucose-based PD solution. An increase in the ultrafiltration volume of 90 mL/day is associated with an 18% reduction in the risk of death [4], which appears to be clinically significant. Based on the Osaka University cohort of patients on PD, the between-subject standard deviation (SD) of the change in the ultrafiltration volume was conservatively estimated at 150 mL (actual between-subject SD of the cohort was 114 mL), and the ratio of the between-subject SD to the within-subject SD was 1:1. We calculated that 30 patients completing the study would provide 90% power (at α = 0.05, two-sided) to detect a 90 mL difference in the ultrafiltration volume between empagliflozin and placebo. The sample size was set at 36 subjects to compensate for potential dropouts.

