### Statistical analysis

Two different analysis sets, namely the full and safety analysis sets (FAS and SAS, respectively), will be used in the study. The FAS will include all study participants who receive at least one dose of the study drug and complete at least one post-baseline examination or assessment. The SAS will include all the study participants who receive at least one dose of the study drug. Analyses of the primary and secondary endpoints excluding adverse events will be conducted in the FAS. Adverse events will be compared between the two groups in the SAS. To assess the effects of empagliflozin versus placebo on the primary outcome, we will use a mixed-effects model for repeated measures (MMRM). The model includes treatment, period, and treatment-by-period interaction as fixed effects and individual as random effects. An unstructured marginal covariance structure will be specified. Secondary endpoints for continuous variables will be estimated in the same manner as described for primary endpoints excluding urine KIM-1. In the case of urinary KIM-1, the analysis using MMRM will be conducted with the absolute value at the end of each period as the dependent variable. Skewed data will be log-transformed before analyses. A list of adverse events will be summarized by tables for each treatment. For sensitivity analyses, we will employ a similar analysis by excluding the data with catheter dysfunction (i.e., drainage volume < 80% of the instilled volume or taking ≥ 20 min to instill the PD solution). A subgroup analysis will be performed using the following factors: age (< 65 years/ ≥ 65 years), sex, presence or absence of diabetes, use of icodextrin-containing PD solution, 24-h urine volume (< 200 mL/ ≥ 200 mL), the glucose load from the peritoneal dialysate (concentration × volume per day, median), the glucose concentration of the drained PD solution on FAST PET (median), and the drained PD solution-to-serum creatinine ratio (median) on FAST PET. Missing data will not be imputed. Statistical analyses will be performed using SAS software (SAS Institute, Cary, NC, USA). Interim analysis will not be conducted.

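### The printed primary model analyses change from each period's baseline with no baseline term, giving up a modest share of precision (about 0–25% of the variance on the plan's own SD ratio)

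*Protocol article*

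**What the plan says.** Under its Primary endpoint heading, the protocol article defines the outcome as follows: "The primary endpoint of the study is the change in the daily ultrafiltration volume from baseline to week 8 in each intervention period". Its design is a "two-period crossover consisting of 8 weeks of treatment and a 4-week washout between treatment periods".

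The model is given under Statistical analysis: "The model includes treatment, period, and treatment-by-period interaction as fixed effects and individual as random effects". On the covariance, the article adds: "An unstructured marginal covariance structure will be specified". No baseline covariate is named. The same model serves the continuous secondary endpoints, which are also changes from baseline. Urinary KIM-1 is the exception and is analysed as an absolute value.

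The article does not say outright that period 2 has its own baseline, and the schedule grid of Table 2 was not available in the text reviewed. The inference rests on three things:

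- The endpoint is defined separately for each period.
- There is a washout, and visits are every 4 weeks.
- A footnote to Table 2 reads "Urine KIM-1 is measured only on Visit 3 and Visit 6". Visits at weeks 0, 4, 8, 12, 16 and 20 make Visits 3 and 6 the two week-8 assessments, and Visit 4 (week 12) the start of period 2.

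**The concern.** In a crossover each participant is already their own control. Subtracting a separate, noisy baseline in each period adds the variability of both baselines to the treatment contrast. A regression on baseline would subtract only the part of the baseline difference that predicts the week-8 difference.

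The treatment-by-period term and the unstructured covariance do not recover the loss, because neither uses baseline information beyond the subtraction. With about 30 completers expected, precision matters. On the period-specific reading the baseline measurements are collected anyway, to compute the change.

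**Working it through.** **Inputs from Sample size calculation (protocol article).** The target is to "detect a 90 mL difference in the ultrafiltration volume between empagliflozin and placebo". For the variance components, "the ratio of the between-subject SD to the within-subject SD was 1:1". As for the size of the SD of the change, it was "conservatively estimated at 150 mL (actual between-subject SD of the cohort was 114 mL"). The plan has 30 completers, two-sided alpha 0.05 and 90% power. No correlation between baseline and week 8 is given.

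**Step 1: the plan's own figure.** A 1:1 ratio of between- to within-subject SD gives a correlation of 0.5 between the two change scores. If 150 mL is the total SD of the change, the SD of the paired difference is 150 × √(2 × (1 − 0.5)) = 150 mL. Then N = ((1.960 + 1.282) × 150/90)² = 29.2, so 30, which matches. Power at 30 is 90.8% by the normal formula and 88.7% by the non-central t (28 df). If 150 mL is instead the within-subject SD, the paired-difference SD is 150 × √2 = 212 mL and power at 30 is 61.2% (t).

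**Step 2: cost of omitting baseline.** Write B and Y for the baseline and week-8 values in periods 1 and 2. Let V be the variance of both B1 − B2 and Y1 − Y2 (taken as equal), and r their correlation.

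- Change-score contrast (Y1 − B1) − (Y2 − B2): variance 2V(1 − r).
- Week-8 contrast adjusted for the baseline difference: variance V(1 − r²).
- Ratio: (1 + r)/2. Avoidable share: (1 − r)/2.

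**Step 3: what the plan implies about r.** With equal variances at each time point, let

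- a = correlation of baseline and week 8 within a period (8 weeks apart);
- b = correlation between periods at the same time point (12 weeks apart);
- d = mean of the two remaining correlations (4 and 20 weeks apart).

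The change-score correlation is (b − d)/(1 − a). Setting it to 0.5 gives d = b − (1 − a)/2. Since r = (a − d)/(1 − b), it follows that 1 − r = (1 − a)/(2(1 − b)), and the avoidable share is (1 − a)/(4(1 − b)).

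If a ≥ b, then r ≥ 0.5 and the share is at most 25%. Examples: a = b gives 25%; a = 0.8, b = 0.7 gives 0.2/1.2 = 17%; a = 0.9, b = 0.7 gives 0.1/1.2 = 8%.

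**Step 4: effect on power with 30 completers.** Non-central t, 28 df unadjusted and 27 df adjusted. The adjusted SD is the unadjusted SD × √((1 + r)/2).

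| Analysis | Avoidable share | SD (from 150 mL) | Power | SD (from 212 mL) | Power |
|---|---|---|---|---|---|
| Change, no baseline | – | 150.0 | 88.7% | 212.1 | 61.2% |
| Adjusted, r = 0.5 | 25% | 129.9 | 95.5% | 183.7 | 73.5% |
| Adjusted, r = 0.7 | 15% | 138.3 | 93.0% | 195.6 | 68.1% |
| Adjusted, r = 0.9 | 5% | 146.2 | 90.1% | 206.8 | 63.3% |

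Simulation (4,000 trials per setting, n = 30, paired-difference SD 150 mL) agreed. The empirical standard errors were 27.0 against 24.1 mL at r = 0.5, and 27.3 against 25.7 mL at r = 0.7. Null rejection with adjustment was 4.8–5.4% over the settings run.

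**Step 5: carryover.** Suppose a residual effect L is present at the post-washout baseline in those given empagliflozin first.

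| Residual L | Bias, change score | Bias, adjusted |
|---|---|---|
| Gone by week 8 of period 2 | +L/2 | about +rL/2 |
| Persists through week 8 of period 2 | 0 | about −(1 − r)L/2 |

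Neither analysis is better in both cases.

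**The case against.** - **Change from baseline is conventional, and the trial is powered for it.** This stands. The 150 mL is described as an SD of the change, so the 30 completers already pay for the baseline noise. A reader might infer that the treatment estimate is biased or the sample size wrong. The documents support neither: without carryover the change-score contrast is unbiased, and the stated N reproduces.
- **The loss could be put much higher.** A reader might infer that up to half the variance is wasted, since r = 0 gives (1 − 0)/2 = 50%. Equal correlation among all four measurements gives r = 0, but it also makes the change-score correlation 0, against the plan's 0.5. Under the plan's ratio, r = 0 needs 1 − a = 2(1 − b), for example a = 0.6 and b = 0.8, so that the closer pair is the less correlated. Correlation decaying by 0.95 per week would give a 42% share, but its change-score correlation is (0.540 − 0.586)/(1 − 0.663) = −0.14, which also conflicts with the plan.
- **Adjustment might be defended as protection against carryover.** That holds only for a residual gone by week 8. The Introduction raises effects on peritoneal fibrosis and angiogenesis, which need not fade quickly, so the opposite case cannot be dismissed.
- **The second baseline is inferred.** This stands as a caveat. A single common baseline would cancel in the within-patient contrast, and the point would fall away.
- **The analysis plan, not shown, may add a baseline term.** Possible. But the article sets out the primary model term by term, and an analysis plan that followed it would have none.

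**Conclusion.** The point holds as one of efficiency. As printed, the primary model uses raw change with no baseline term and gives up (1 − r)/2 of the variance of the treatment contrast. On the plan's 1:1 ratio this is roughly 0–25%, worth between 1.4 points of power (88.7% to 90.1%, r = 0.9) and 6.8 points (to 95.5%, r = 0.5) at a paired-difference SD of 150 mL. If that SD is 212 mL, power rises from 61.2% to at most 73.5%.

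This rests on four assumptions: period-specific baselines; equal variances; the 1:1 ratio describing the two change scores; and values 8 weeks apart correlating at least as well as those 12 weeks apart. The 25% ceiling depends on the last two, and there is no useful floor, since the share tends to zero as r approaches 1. The change is worth making because it is cheap. The planned analysis would still be valid without it.

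**What to change.** Before unblinding, state in the protocol or analysis plan that the primary MMRM includes the period-specific baseline daily ultrafiltration volume as two covariates: the participant's mean of the two period baselines, and the deviation of each period's baseline from that mean. The split matters, because the raw baseline alone in a random-individual model mixes between- and within-patient slopes. The response can stay as change; with both covariates in the model, the treatment estimate is the same as with the week-8 value. Say how a participant with only one period baseline is handled. Do the same for the continuous secondary endpoints that have a baseline. Confirm in the text that period 2 has its own baseline.

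Keep the unadjusted change-score model as a sensitivity analysis, since it is the one that cancels a residual effect persisting through period 2.

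Cost: a sentence or two, about one residual degree of freedom, and the bias of about −(1 − r)L/2 if such an effect exists. No new data are needed.
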